## Abstract

Photobiomodulation is a safe option for controlling pain, edema, and trismus when applied postoperatively in third molar surgery. However, administration prior to surgery has been under-explored. This study aims to explore the effectiveness of pre-emptive photobiomodulation in reducing postoperative edema in impacted lower third molar extractions. Two groups of healthy individuals undergoing tooth extraction will be randomly assigned: Control group receiving pre-emptive corticosteroid and simulated photobiomodulation, and Photobiomodulation Group receiving intraoral low-intensity laser and extraoral LED cluster application. The primary outcome will be postoperative edema after 48 h. The secondary outcomes will be pain, trismus dysphagia, and analgesic intake (paracetamol). These outcomes will be assessed at baseline as well as two and seven days after surgery. Adverse effects will be recorded. Data will be presented as means ± SD and a p-value < 0.05 will be indicative of statistical significance.

## Introduction

The extraction of impacted lower third molars is a very common procedure that has been technically standardized since the early 20^th^ century [1]. However, it remains associated with a high degree of postoperative discomfort, primarily related to pain, swelling, trismus, and dysphagia [1, 2].

To minimize these unpleasant effects on patients’ quality of life, various pharmacological and non-pharmacological measures with varying degrees of clinical effectiveness have been recommended [1, 3]. Pharmacological measures include the use of analgesics, antibiotics, and anti-inflammatory drugs, primarily corticosteroids [1, 3–7]. Some authors have suggested the pre-emptive use of anti-inflammatory drugs for controlling postoperative pain and swelling following third molar extractions [8–11]. However, there is no definitive evidence with regards to the benefits of prophylactic use, which has been associated with numerous side effects, such as hyperglycemia, insulin resistance, the development of glucocorticoid resistance, hypertension, muscle atrophy, lipid deposition abnormalities, interference with normal healing, an increased risk of infection, mood disorders, cardiovascular complications, and osteoporosis [12–14]. Therefore, the restriction of the use of such drugs is essential, especially in prolonged periods [14, 15]. Non-pharmacological resources include cryotherapy, ozone therapy, growth factors, and photobiomodulation [1, 16].

Photobiomodulation has proved to be a viable option when applied postoperatively in third molar surgeries to control pain, swelling, and trismus, both with wavelengths in the red and infrared spectrum when used separately [17, 18]. Thus far, however, the combined use of wavelengths in both ranges of the light spectrum prior to surgery has not been sufficiently investigated [19, 20]. Given the promising results demonstrated by photobiomodulation, probably the preoperative application of red and infrared laser and LED (both extraoral and intraoral) is expected to be effective in reducing postoperative swelling in retained lower third molar extractions.

Thus, the aim of the proposed study is to investigate the effectiveness of pre-emptive photobiomodulation in reducing post-operative edema following the extraction of impacted lower third molars.

## Methods

### Study design

This randomized, controlled, double-blind clinical protocol is in accordance with the criteria for clinical study design as per the SPIRIT Statement. It has been submitted to the Human Research Ethics Committee of the Catholic University of Uruguay (process: 220420). After a verbal and written explanation of the study, volunteers who agree to participate will sign a statement of informed consent. All patients will have the option to withdraw from the study at any time. The study will be conducted in accordance with the Declaration of Helsinki. The treatments will be carried out at the Dental Surgical Clinic of the University Health Clinic (Apolônia) at the Catholic University of Uruguay from November 2023, to July 2024. Any complications or changes will be investigated and reported to the Research Ethics Committee. The project has been registered on the Clinical Trials platform (www.clinicaltrial.gov), registration number: NCT05924191. The data resulting from its development will be stored in an anonymized manner at the Open Science Framework repository. The files will be posted on the already created link (https://doi.org/10.17605/OSF.IO/3EVMR).

### Sample size calculation

The sample size was calculated to provide an 80% power (α = 0.05). The sample size will consist of 30 surgeries per group. Thirty patients with bilateral and symmetric lower third molars (right and left) will be selected. The procedure will then be performed randomly (split-mouth design), totaling 60 surgeries (30 surgeries in the control group and 30 surgeries in the experimental group). For the calculation, we used the 48-hour time point in the article by Aras and Güngörmüş (2010) [21]. The average edema measurement was 105 mm in the control group and 109 mm in the experimental group. The larger standard deviation between the two means ±5 mm was chosen for the sample size calculation.

### Calibration and examiner training

The examiner who will conduct the pre-operative measurements (considered the gold standard) will lead the calibration process for the researchers who will perform the post-operative assessments. Joint training and calibration exercises will be carried out three times, and the data will be discussed among these researchers and the gold standard examiner to achieve an acceptable level of agreement using the Intraclass Correlation Coefficient (ICC) test [22]. Subsequently, the examiners will individually perform the proposed assessments in the study on 10 adult volunteers at different times. These patients will not be part of the sample. Reliability will be determined using the intraclass correlation coefficient (ICC) [22].

### Laser’s safety methodology

A course conducted by qualified professionals will provide comprehensive laser safety training for all researchers, ensuring the safe use of lasers. The laser devices in this study are Class 3b (power varies between 5–500 mW). This category of lasers can cause accidental harm if looked at directly. All participants and researchers will use protective eyewear during the applications and simulations.

### Participant characterization

Participants referred to the Oral and Maxillofacial Surgery and Traumatology service of the Catholic University of Uruguay, who need to undergo the extraction of impacted lower third molars, will be assessed. The selection of cases will be based on the surgical difficulty of the procedure and anatomical position. The molars will be classified according to Pell and Gregory Classes II or III and/or B or C; vertical or mesioangular position, following Winter’s classification, or Class II with the need for osteotomy, or Class III with the need for osteotomy and tooth sectioning, based on the Prant Scale modified by Amarillas-Escobar et al (2010) [23], which is used to assess the difficulty of the dental extraction procedures.

Individuals eligible for inclusion*—*will need to have two impacted lower third molars, with inclusion based on the surgical difficulty of the procedure and anatomical position as described in the Participant Characterization section. There should be a clear indication for third molar extraction, whether due to recurrent infections, malposition, orthodontic recommendation, or a professional recommendation provided in writing. Male and female individuals between 18 and 50 years of age without any comorbidities will be eligible. The individuals should also maintain good oral hygiene to be considered for the study.

Exclusion of individuals—if they have local conditions that contraindicate surgical intervention or could complicate the post-operative period, such as acute pericoronitis in the previous 30 days or temporomandibular joint ankylosis. Smokers, individuals lacking both upper and lower central incisors, those with a history of photosensitivity, pregnant or lactating women, and individuals using anti-inflammatory drugs or analgesics and those with allergies to any drugs used in the study (e.g., paracetamol, 2% chlorhexidine, local anesthetics, sodium bisulfite) will also be excluded. Individuals experiencing surgical complications, such as bleeding or operative difficulties, will be ineligible for the study due to the potential impact on maintaining the expected surgical standards and the accuracy of the study outcomes. Participants undergoing surgical procedures lasting longer than 90 minutes will be excluded from the study. Surgeries lasting longer than 90 minutes could potentially impact the accuracy and reliability of the findings due to the likelihood of increased post-operative trauma, which may result in more significant edema and pain.

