### Study outcomes

The primary outcome of the study will be:

Edema—three measurements will be taken on the patient’s face with a previously sanitized flexible measuring tape: tragus-pogonion, tragus-labial commissure, and mandibular angle-outer orbital commissure [26]. Measurements will be taken immediately before surgery as well as two and seven days after surgery.

The secondary outcomes of the study will be:

Pain Sensitivity*—*The visual analog scale (VAS) is the most widely used instrument for measuring postoperative pain after oral surgeries with photobiomodulation in the postoperative period [24, 26]. In this study, the VAS will be used immediately after surgery as well as two and seven days after surgery [24, 26] using 10-cm line with "0" (no pain) at one end and "10" (unbearable pain) at the other. Instructions on marking will be provided to the patient by the same operator.

Quantity of pain tablets taken during the period*—*The number of analgesic tablets taken at two and seven days will be counted. All participants will take paracetamol and be instructed to take it every six hours only in the presence of pain [27]. At the beginning of the study, each participant will be provided a paracetamol tablet, which is a drug with purely analgesic effects [28]. At the end of the experiment, the quantity of tablets will be evaluated as a secondary outcome. Patient adherence will be monitored. For such, the patients will be asked to bring the medication blister pack to the appointment to check how it is being used.

Postoperative trismus assessment*—*Spasms in the masticatory muscles (trismus) can limit or even prevent mouth opening after the surgical removal of impacted third molars [21, 23, 29]. This outcome is typically evaluated by measuring the distance between the incisal edges of the upper and lower central incisors using calipers [27, 29]. In this study, previously calibrated evaluators will measure mouth opening in each patient before surgery as well as two and seven days after surgery.

Impact of the surgical procedure on quality of life*—*Two previously calibrated evaluators will ask patients to respond with "yes" or "no" to the following 10 questions two and seven days after surgery, as described by Sierra et al. (2013) [26] and Sierra et al. (2015) [24].

The 10 questions were:

Are you maintaining your social activities normally?

Are you working/studying normally?

Are you maintaining your regular diet?

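### Read literally, the incisor exclusion leaves eligible a patient who lacks only the upper or only the lower central incisors, in whom the trismus distance cannot be measured

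*Protocol article*

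**What the plan says.** In the Participant characterization section of the protocol article, the list of exclusions includes "individuals lacking both upper and lower central incisors". The inclusion criteria in the same section say that candidates "will need to have two impacted lower third molars". They add conditions on surgical difficulty, indication, age, comorbidity and oral hygiene, and none concerns the incisors.

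Under Study outcomes, trismus is described as typically evaluated by "measuring the distance between the incisal edges of the upper and lower central incisors using calipers". For this trial the text then says that "previously calibrated evaluators will measure mouth opening in each patient before surgery as well as two and seven days after surgery". It names no other method and no alternative landmark. The Abstract lists trismus among the secondary outcomes; the primary outcome is edema at 48 hours.

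**The concern.** An interincisal distance has two ends, one in each arch, and is undefined if either end is missing. The rule meant to secure it should therefore exclude a patient when either set is absent. As worded, it joins the two absences with an *and*, so it applies only when both sets are absent. Nothing else in the outcome list uses the incisors, so protecting the trismus measure is the evident purpose of the exclusion. On its literal wording the rule does not achieve that purpose.

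What is at stake is whether one secondary outcome can be measured in everyone who enters. The plan promises a mouth-opening value for each patient at each visit. For a patient without one of the two sets, the evaluator would have to leave the value blank or measure from some other point, which is a different quantity. Because each patient supplies both the control and the experimental surgery, a blank removes a whole pair from the trismus comparison.

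**Working it through.** The protocol states no figure for this point, so the check is one of logic, followed by simple arithmetic on the consequence.

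**Inputs**
- Exclusion wording: Participant characterization.
- Trismus method and visits (before surgery, day 2, day 7): Study outcomes.
- Two surgeries in each of 30 patients: Sample size calculation ("The sample size will consist of 30 surgeries per group", split-mouth) and Randomization.

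**Step 1: the rule against the measure.** There are four possible cases. Here *absent* means that no central incisor remains in that arch.

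| Upper central incisors | Lower central incisors | Distance measurable? | Excluded on the literal wording? |
|---|---|---|---|
| present | present | yes | no |
| absent | present | no | no |
| present | absent | no | no |
| absent | absent | no | yes |

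The measure fails in three of the four cases and the exclusion removes one of them. The two middle rows are the gap: eligible, but not measurable.

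**Step 2: does anything else close the gap?** The inclusion criteria do not mention incisors. The trismus paragraph gives no fallback landmark. The Calibration and examiner training section covers agreement between examiners and does not address missing teeth.

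**Step 3: cost per affected patient, if the value is left missing.**
- Readings lost: 2 surgeries × 3 time points = 6, out of 30 × 6 = 180; 6/180 = 3.3%.
- Pairs lost: 1/30 = 3.3%.
- Standard error of the mean paired difference, with an unchanged standard deviation: multiplied by √(30/29) = 1.017, an increase of about 1.7%.

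**Step 4: how many such patients?** The documents give no prevalence, so the number is unknown and zero is possible. The total loss is the Step 3 cost multiplied by a count that cannot be derived here.

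**Step 5: other quantities.** The sample size rests on edema (105 against 109 mm, SD 5 mm). Edema is taped between facial landmarks that do not involve the incisors. Neither is affected.

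**The case against.** The strongest reply is that the phrase can be read as intended: lacking both may mean not having the complete pair, and then there is no gap. The evident purpose of the rule favours that reading. This stands as a reason to treat the matter as wording and not as a deliberate design choice. It does not remove the point, because those who screen patients apply the text in front of them and the plain reading of *both … and* is the narrower one.

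A second reply is that the article only says trismus is typically measured this way, so the method for this trial is implied and not fixed. That is fair, but no other method is given, and an incisor exclusion would have no purpose if another were intended.

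A third reply is that few such patients will present, given ages 18 to 50, no comorbidities and good oral hygiene. That is plausible, and it limits the weight of the point.

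Two stronger readings are tempting, and the documents support neither.

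- A reader might infer that a substitute landmark would carry its error straight into the change from baseline. That holds only if the landmark varies between visits. One used consistently would largely cancel in a within-patient change. The pre-operative and post-operative examiners do differ, but they are trained and calibrated together, so visit-to-visit improvisation is conjecture.
- A reader might infer bias in the treatment comparison. Under the split-mouth design the same patient provides both treatments, so missing incisors affect both alike and give no evident reason for bias.

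The absence of a form field recording which teeth were used is operational detail that an article may leave to the full protocol. It is not raised as a fault.

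**Conclusion.** The point holds as a wording error in one eligibility rule. Read literally, the exclusion does not match the only trismus method stated, and it admits patients in whom that measurement cannot be taken.

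Its size is small: one of 30 pairs (3.3%) for the trismus comparison per such patient, in an unknown number of patients that may be zero. The expected consequence is a slight loss of precision on one secondary outcome.

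The conclusion rests on two assumptions: that the exclusion is applied as written, and that the interincisal distance is the measure this trial will use. If screening staff already read the rule protectively, nothing is lost and the correction only makes the text say what is meant.

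**What to change.** Reword the exclusion to *individuals lacking the upper or the lower central incisors*, with the explicit meaning that at least one upper and one opposing lower central incisor must be present. The two middle rows of the table then become excluded, and the entry rule matches the trismus measurement.

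The cost is a change of a few words in one criterion. It needs no change to the sample size, the randomization or any other outcome. If such patients are as few as their age and health suggest, the effect on recruitment is negligible.

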### Randomization

We will use a random sequence generator program (https://www.sealedenvelope.com/) to assign participants to the two experimental groups. Randomization will involve 30 participants. Each participant will undergo two surgeries–one on each side. The first surgery will be performed on the right side and treatment for the left side will be the opposite of the randomized treatment, ensuring no repetition of identical treatments in the same patient. A third party not otherwise involved in the study will handle sequence generation and envelope preparation. Opaque envelopes labeled with sequential numbers will contain a sheet specifying the group for the first surgery based on the generated sequence. These envelopes will remain sealed and stored securely in numerical order until the surgeries.

The patients will undergo assessments by the surgeons and, upon meeting the previously described eligibility criteria, will be enrolled in the study. All participants will be submitted to the same surgical protocol. Just prior to the surgeries, the researcher responsible for photobiomodulation application will open an envelope (without changing the sequence of the remaining envelopes) and perform the procedure indicated.

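### The first operation is always on the right, so side and surgery order form one factor; the paired analysis should carry a term for it

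*Protocol article*

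**What the plan says.** The trial is split-mouth: "Randomization will involve 30 participants", and each has both lower third molars removed in two operations. The Randomization section fixes the order: "The first surgery will be performed on the right side and treatment for the left side will be the opposite of the randomized treatment". The sheet in each envelope "will contain a sheet specifying the group for the first surgery based on the generated sequence". What is randomised is therefore the treatment sequence, while side and order are fixed.

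On how the list is built, the article says "We will use a random sequence generator program" and names the service. It gives no block structure and does not say whether the two sequences are to be equal in number.

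The Statistical analyses section lets normality checks decide the tests. The only model term it names is the interaction of treatment with sex. Edema is measured before surgery and at two and seven days (Study outcomes), with 48 hours as the primary time point (Abstract).

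**The concern.** Two nuisance influences coincide in every patient. One is the side of the mouth. The other is order: at the second operation the patient has already been through one extraction. Blinding to treatment does not hide either of them.

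Each patient contributes one difference between treatments. If the right/first operation gives systematically different swelling from the left/second one, that shift enters the difference with a plus sign in one sequence and a minus sign in the other. An analysis that does not know the sequence treats this as random noise. The planned difference is only 4 mm, so a shift of a few millimetres would be noticeable.

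The sequence is recorded and randomised, so the information needed to remove the shift is already in the trial. What is at stake is precision, and protection of the estimate if the analysed sequences are unequal. Pain scores and tablet counts could be affected in the same way, but the article gives no figure for the size.

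**Working it through.** **The plan's own figure.** Inputs from Sample size calculation: "The sample size was calculated to provide an 80% power (α = 0.05"); "The average edema measurement was 105 mm in the control group and 109 mm in the experimental group", a difference of 4 mm; and "The larger standard deviation between the two means ±5 mm was chosen for the sample size calculation". Two-sided testing is assumed. For independent groups, n = 2(1.960 + 0.842)² × 5²/4² = 24.5, so 25 per group (26 with the t distribution). The article states "The sample size will consist of 30 surgeries per group"; 30 per group gives about 86% power (t). The stated 30 is not reproduced without an unstated allowance. That is a separate matter, and nothing below depends on it.

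**Model.** Let d be the photobiomodulation side minus the control side in one patient, τ the treatment effect, p the right/first minus left/second shift, and SDd the SD of d without the shift.

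- Photobiomodulation first (right): d = τ + p + error
- Photobiomodulation second (left): d = τ − p + error

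**SDd.** The article's 5 mm is the SD of a group's measurements, not of a within-patient difference, and no correlation ρ is given. SDd = 5√(2(1 − ρ)) is 7.07 mm at ρ = 0 and 5 mm at ρ = 0.5. Both values of ρ, and all values of p, are assumptions.

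**Effect on the error term.** If the sequence is ignored, the variance of d is about SDd² + p².

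| p (mm) | Increase, ρ = 0: p²/50 | Increase, ρ = 0.5: p²/25 |
|---|---|---|
| 1 | 2% | 4% |
| 2 | 8% | 16% |
| 3 | 18% | 36% |

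For p = 2 mm this equals working with 30/1.08 = 27.8 or 30/1.16 = 25.9 pairs.

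**Effect of unequal sequences.** The plain mean of d estimates τ + p(n1 − n2)/30. At 18/12 the shift is 6p/30 = 0.20p; at 20/10 it is 10p/30 = 0.33p. If allocation were unrestricted (an assumption), a Binomial(30, 0.5) gives exactly 15/15 with probability 0.14, 18/12 or worse with 0.36, and 20/10 or worse with 0.10.

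**One loss or two?** Under unrestricted allocation the variance of (n1 − n2)/30 is 1/30, so the shift has variance p²/30. That is exactly the extra p² in Var(d) divided by 30. The inflated error and the shift are one quantity, seen unconditionally and conditionally.

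**Size and power for a 4 mm difference** (20,000 simulations per figure).

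| Situation | p (mm) | Shift (mm) | Alpha, ρ = 0 / 0.5 | Power, ρ = 0 / 0.5 |
|---|---|---|---|---|
| 15/15, term included | any | 0 | 0.05 / 0.05 | 0.85 / 0.99 |
| 15/15, term omitted | 2 | 0 | 0.043 / 0.038 | 0.83 / 0.98 |
| 15/15, term omitted | 3 | 0 | 0.036 / 0.025 | 0.81 / 0.97 |
| 20/10, term omitted | 2 | 0.67 | 0.07 / 0.09 | not comparable |
| 20/10, term omitted | 3 | 1.00 | 0.09 / 0.12 | not comparable |
| 20/10, term included | any | 0 | 0.05 / 0.05 | 0.81 / 0.98 |

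Power is not comparable in the two shifted rows because the estimate itself is displaced. Averaged over unrestricted randomisation, the test without the term had alpha 0.048 to 0.050.

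**Price of the term.** With the term, the variance of the treatment estimate is (SDd²/4)(1/n1 + 1/n2). Relative to 15/15 (SDd²/30) it is the same at 15/15, 4% larger at 18/12 and 12.5% larger at 20/10. The critical t value moves from 2.045 (29 df) to 2.048 (28 df).

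**The case against.** A reader might infer that the right-first rule biases the treatment comparison. The documents do not support that. The treatment of the first operation is randomised and the other side receives the opposite, so treatment is balanced over the factor in expectation. Averaged over randomisation, the paired test without the term is unbiased and holds its level. With 15/15 sequences the shift is exactly zero, and the test without the term is merely conservative.

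Nor does it matter for this trial that side and order cannot be separated. Neither is a target of estimation, and because they coincide a single term removes both.

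A reader might also infer that the list is unblocked and the analysis unadjusted. The article states neither. Block structure and covariates are commonly left to the full protocol or analysis plan, so these are points to confirm and cannot be called missing.

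The size is also modest. At correlation 0.5, power for 4 mm stays at 97% or more for shifts up to 3 mm with balanced sequences. The article requires symmetric bilateral molars, uses one surgical protocol and measures edema before each operation, all of which should reduce p. These objections all stand. They remove any claim of bias by design, but not the case for a term that costs almost nothing.

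**Conclusion.** The point holds as a cheap improvement in precision and robustness, not as a design error. The stated rule makes side and order one factor in all 30 patients. If the analysis ignores it, the variance of the within-patient difference rises by p²: 2% to 18% at correlation 0, or 4% to 36% at correlation 0.5, for shifts of 1 to 3 mm. If the analysed sequences are unequal, the estimate is displaced by p(n1 − n2)/30, which is this same loss viewed conditionally.

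The conclusion on the rule rests on the article's text. The sizes rest on assumed values of p and of the within-patient correlation, and the imbalance probabilities on assumed unrestricted allocation.

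Even a balanced list may not stay balanced. The eligibility section excludes patients for surgical complications or operations over 90 minutes, and the Experimental design section excludes those who miss visits or take other drugs. That section also says that all participants' data will be analysed, so the effect on balance depends on how the two statements are reconciled. The sequence term protects in either case.

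**What to change.** Keep the right-first rule and state three things:

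1. The primary analysis of 48-hour edema uses within-patient differences between the two treatments, with sequence (photobiomodulation first or second, coded +1/−1) as a fixed term. The treatment estimate is then the unweighted average of the two sequence means of d.
2. The continuous secondary outcomes (VAS pain, mouth opening and, if treated as continuous, tablet count) are analysed in the same way.
3. The randomisation list is blocked so that 15 patients fall in each sequence. If the list already is, confirm it.

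The term alone removes both the inflated error and the conditional shift. Blocking alone removes the shift at the point of allocation but leaves the inflated error; together with the term it avoids the efficiency loss. Randomising the starting side as well is not needed: it would create two nuisance factors in place of one without helping the treatment estimate.

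The cost is one degree of freedom and a small loss of efficiency if sequences end up unequal (4% in variance at 18/12, 12.5% at 20/10). No extra data or patients are needed.
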